## Abstract

**Background:**

Available guidelines on the management of upper tract urothelial carcinoma (UTUC) are restricted due to the lack of strong evidence–based recommendations. Adequate, well-powered randomized trials are missing due to the rarity of the disease. To overcome this problem, we need alternative study designs to provide generalizable data.

**Objective:**

The primary aim of this registry is to provide a real-world overview on patterns of presentation and management of UTUC. Secondary objectives include comparison of outcomes of different treatments and tumor stages and evaluation of compliance with the current European Association of Urology recommendations for UTUC.

**Methods:**

For this observational, international, multicenter, cohort study, clinical data of consecutive patients suspected of having UTUC, irrespective of type of management, will be prospectively collected up to 5 years after inclusion. Data on the patterns of presentation, diagnostics, and treatment as well as short-, mid-, and long-term oncological and functional outcomes will be analyzed. Possible associations between variables, basal characteristics, and outcomes will be tested by multivariable analyses. The methodology will address potential sources of bias and confounders.

**Results:**

The registry was initiated in November 2014 after obtaining institutional review board approval. Data collection started in December 2014. At the time of submission of this manuscript, 2451 patients from 125 centers from 37 countries were included. Inclusion of patients will be closed 5 years after initiation of the registry. Quality checks will be performed centrally with continuous communication and feedback with the centers to ensure accuracy. The first results are expected in the first trimester of 2020.

**Conclusions:**

This large observational prospective cohort will generate landmark “real-world” data and hypotheses for further studies. We expect these data to optimize the management of UTUC, provide insights on harms and benefits of treatment, and serve as quality control.

**Trial Registration:**

ClinicalTrials.gov NCT02281188; https://clinicaltrials.gov/ct2/show/NCT02281188.

**International Registered Report Identifier (IRRID):**

DERR1-10.2196/15363

## Introduction

### Background

Upper tract urothelial carcinomas (UTUCs) have a low prevalence, with an estimated annual incidence of 2 per 100,000 inhabitants in Western countries [1]. Most of them are urothelial cell carcinomas arising from the lining endoluminal urothelium, and they represent 5%-10% of all urothelial carcinomas [1]. At diagnosis, nearly 60% of UTUCs are found to be invasive, a much higher percentage than the 15%-20% reported for its sibling tumor in the bladder [1,2]. Although the general genotype of UTUC is similar to its bladder counterpart, it is different in its genetic expression and frequency by stage [3-5]. UTUC may present in a primary isolated form in the upper urinary tract or secondary form after a primary diagnosis of bladder urothelial carcinoma. Synchronous upper and lower urinary tract urothelial carcinoma has been reported in up to 17% of cases [6].

Irrespective of whether it is because of advanced diagnostic methods utilization, decreased competing death causes, or real increasing incidence, the rate of invasive UTUC tumors (>pT1) at diagnosis has been increasing in recent years [1,6]. Metastases are found in 7% of all patients with UTUCs. The 5-year survival does not reach 50% for patients with pT2/pT3 UTUCs and is lower than 10% for pT4 tumors [7,8].

The European Association of Urology (EAU) guidelines recommend risk stratification of UTUC in low- and high-risk disease, based on clinical and pathological factors. These include focality and size of the tumor, presence of high-grade urinary cytology or high-grade histology on biopsy, imaging characteristics, and presence of previous radical cystectomy for bladder cancer or variant histology [1,7]. This risk classification is intended to drive treatment, and some of these risk factors, either isolated or integrated, have prognostic implications [7-9].

The gold standard of UTUC remains radical nephroureterectomy (RNU) with complete bladder cuff excision [10,11]. However, there is a growing interest in minimally invasive, kidney-sparing approaches by ureterorenoscopy (URS). This shift in treatment management is fueled by the development and evolution of flexible instruments. Indications for kidney-sparing management are discussed in detail in the current guidelines and should be considered in patients with low-risk disease [1,7,12]. A particular challenge during endoscopic management is appropriate grading and staging of tumors, both necessary for accurate risk assessment, which is essential for successful therapeutic management [1,13].

Rates of recurrence, either distant or local, are correlated with various factors, the most important of which are pathological stage and grade. A common site of recurrence after treatment of UTUC is the bladder. Intravesical recurrence following RNU is a common problem, with an incidence of nearly 20%-50% [1]. In a meta-analysis (4057 participants) assessing the impact of diagnostic URS prior to RNU, a strong correlation was found between previous URS and development of intravesical recurrence during follow-up after RNU (hazard ratio=1.53, *P*<.001) [10]. Tumor location also plays a role in the choice of therapy based on anatomic location [1,6,14].

### Rationale for a Clinical Registry

Available clinical information on the management of UTUC relies mainly on historical cohorts. Monocentric data from merging international databases or population-based studies have provided the highest level of evidence so far and are challenging the standard management algorithms [15-17]. Although valuable, this type of information is prone to bias. Patient selection criteria, attrition bias, and verification bias are among the most frequent confounders in spite of efforts to adjust for them. Even in large cohorts, confounding variables cannot be completely corrected for. Although associations may be observed, they rarely confirm causality and may have unknown effects [18,19].

In an intent to increase the quality of evidence, systematic reviews and meta-analysis have explored specific UTUC outcomes of distinct treatment modalities as well as predictive and prognostic factors [19-27]. Obviously, they provide insights in the natural history of UTUC, but they are still the product of a low-evidence report. Therefore, they do not result in strong recommendations due to the flaws in accuracy and generalizability [28].

Although randomized trials (RCTs) would provide sound answers, the rarity of the condition prevents studies from obtaining an adequately powered sample size for correct comparison in a reasonable study time. The late onset and comorbidity of the affected population will limit inclusion and likely preclude generalizability of RCT results. In this scenario, it is rational to rely on alternative study designs that allow rapid data collection with inclusion of a large population with a broader geographic and ethnic spectrum [29,30].

Clinical registries are defined as “a system that collects a defined minimum data set from patients undergoing a particular procedure, diagnosed with a disease or using the health care resource” [29]. They are observational databases focusing on a specific clinical condition, therapy, or population without specific mandate approaches and are intended to reflect “real world” practice in a large population. When properly designed and executed, they serve to improve the quality of health care and as hypothesis generators [29].

Very little is known about the prevalence of registries worldwide. Overall, the interest has increased rapidly in the last decade in countries such as the United States, Sweden, and the United Kingdom, with more than 100 registries per country. Whether named registries, quality registries, clinical databases, clinical audits, or quality improvement programs, the medical societies unanimously recognized their value in the clinical research context [31,32].

We hereby present the design of the Clinical Research Office of the Endourology Society (CROES)-UTUC registry.

### Objectives

Overall, the registry aims to provide a contemporary real-world overview and generalizable comparative outcomes on the incidence and management of UTUC across the globe. The CROES-UTUC registry focusses primarily on incidence, indications, treatment, and patient outcomes. When possible, comparative clinical effectiveness of different interventions and assessment of safety of these interventions will be performed.

The primary objective is to describe contemporary patterns of presentation, practice, and treatment of UTUC according to geographic characteristics.

The secondary objectives identified by the steering committee during the design of the registry include several short- and long-term comparative outcomes listed below:

To assess the compliance with the current EAU guidelines on UTUC recommendationsTo assess the validity of risk stratification, as recommended by the current EAU guidelines on UTUCTo assess the intra- and postoperative complications stratified by type of treatmentTo determine the rates and type of recurrences (upper tract and bladder/local or distant) as well as risk factors for patients presenting with primary UTUC stratified by type of treatment (kidney-sparing treatment vs radical nephroureterectomy vs segmental ureterectomy), stage at presentation, select clinicopathologic characteristics, and genderTo determine comparative overall survival stratified by type of treatment and stage at presentation.

## Methods

### Study Design

This is an observational, international, multicenter, cohort study, prospectively collecting clinical data on consecutive patients with UTUC. The registry is set up by the CROES, and its design follows the recommendations of the Agency for Healthcare Research and Quality (US) of 2014 for design and use of patient registries for scientific, clinical, and health policy purposes [29].

This registry collects clinical data on patients with UTUC, irrespective of onset, location, or type of treatment. It enrolls patients at the moment of their health care visits and includes baseline information on demography, symptoms, risk factors, and laboratory variables. Diagnostic procedures are captured as well as management, treatment, and follow-up details (up to 5 years after inclusion). In summary, it captures patterns of presentation, diagnostics, and treatment as well as short-, mid-, and long-term oncological and functional outcomes. The operational flow diagram design of the registry is provided in Figure 1. Patients were not involved in the design of the registry.

Version 2 of the protocol was registered in September 2014 in Clinical trials.gov (trial registration: NCT02281188). The data and material for this study are available from CROES upon request.

A steering committee composed of six international experts in the field oversaw the design process and checked the structure of the registry. Primary and secondary objectives were defined before design and initiation of the registry. The different centers have the opportunity to identify “ad hoc” secondary objectives and propose studies across the duration of the study. The steering committee will review the different study proposals; modify the proposal, if necessary; and consequently approve or deny them. Proposals will be handled according to chronological submission.

Due to the amount of data and the opportunity for the centers to propose studies, not all secondary objectives were predefined prior to initiation of the registry. They will be identified “ad hoc” by the participating centers or the steering committee according to the data available at the time of study proposal. We foresee that the large sample size will allow for comparative studies on benefit of interventions, evaluation and definition of risk factors for recurrence, as well as associations and quasi-randomized outcomes comparisons.

**Figure 1 figure1:**
[figure not shown]
Operational flow diagram of the CROES-UTUC (Clinical Research Office of the Endourology Society for urothelial carcinomas of the upper tract) registry. Colors indicate the different levels of data input, management, and output as well as the interaction directions among them. Green color indicates external sources of information (participating centres); blue colour indicates central registry office tasks; pink/blue color indicates a combination of centres and central office registry output. IRB: institutional review board.

### Participant Characteristics

Adult patients (age≥18 years) suspected of having UTUC either as primary onset or after previous bladder urothelial cancer (during follow-up) and scheduled to undergo any type of diagnostic instrumentation of the upper urinary tract or any surgical treatment (ie, RNU, kidney sparing surgery by URS or percutaneous treatment or segmental ureter or pelvic resection with or without any other neoadjuvant, perioperative, or adjuvant interventions) will be included in the registry. In line with the design and objectives of a registry, the inclusion criteria are broad, while the exclusion criteria are minimized.

No direct benefits or risk for patients are derived from the participation in the registry. The registry data do not imply any change in management policy or practice apart from the standard practice in the respective centers at any moment of the diagnostic and therapeutic follow-up processes.

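### The registry is described as covering every type of management, but its entry rule requires scheduled upper-tract instrumentation or surgery, so treatment shares are conditional on that rule

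*Protocol article*

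**What the plan says.** The protocol article describes its population in three places.

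- **Abstract, Methods:** "clinical data of consecutive patients suspected of having UTUC, irrespective of type of management, will be prospectively collected".
- **Methods, Study Design:** "This registry collects clinical data on patients with UTUC, irrespective of onset, location, or type of treatment".
- **Methods, Participant Characteristics:** the eligibility rule. Beyond adult age and suspicion of UTUC, the patient must be "scheduled to undergo any type of diagnostic instrumentation of the upper urinary tract or any surgical treatment". The parenthesis after it lists surgical and endoscopic procedures. Other therapy appears only as an accompaniment, "with or without any other neoadjuvant, perioperative, or adjuvant interventions". The same section calls the inclusion criteria broad.

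Under Objectives, the primary aim reads: "The primary objective is to describe contemporary patterns of presentation, practice, and treatment of UTUC according to geographic characteristics". The overall aim is wider still, a "contemporary real-world overview and generalizable comparative outcomes on the incidence and management of UTUC across the globe". Neither is restricted to patients scheduled for a procedure, and the Discussion does not name the restriction as a limitation.

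**The concern.** The scope statements and the eligibility rule cannot both hold. A patient suspected of UTUC on imaging or cytology, and then managed with no upper-tract instrumentation and no surgery, falls inside the first and outside the second.

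In a comparison of two operations this would matter little. Here management is itself the primary outcome to be described. A reader who takes the all-management wording at face value will read the registry's treatment shares as shares of all suspected UTUC, and its guideline compliance as compliance across all such patients. Both are in fact computed among patients already selected for a procedure. Adjustment among enrolled patients cannot bring back people who were never enrolled. The registry is also justified partly by the argument that age and comorbidity keep patients out of randomized trials, and patients judged unfit for any procedure are among those this rule leaves out.

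**Working it through.** The plan has no figure of its own to reproduce: it gives no estimate of the excluded fraction, and the target of up to 3000 patients has no stated derivation. The check has two parts.

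**1. Who can enter, reading the rule literally.** The two procedural conditions are joined by *or*.

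| Patient with suspected UTUC | Within the scope in the abstract and Study Design? | Eligible under Participant Characteristics? |
|---|---|---|
| Scheduled for surgery, with or without other therapy | Yes | Yes |
| Scheduled for diagnostic instrumentation, later not operated on | Yes | Yes |
| Scheduled for neither (for example systemic therapy alone, observation or palliation) | Yes | No |

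The conflict is confined to the last row.

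**2. Effect on a treatment share.** Let f be the fraction of the stated population scheduled for neither. Let s be the true share, in that population, of a pathway that does involve instrumentation or surgery.

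- Registry share = s / (1 - f), so the inflation factor is 1 / (1 - f).
- True share = registry share × (1 - f).
- Patients not recorded for every 3000 enrolled = 3000 × f / (1 - f).

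The values of f and the registry share of 60% are assumptions for illustration. Only the 3000 comes from the article (Results).

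| Assumed f | Inflation factor | True share if the registry shows 60% | Shift (points) | Not recorded per 3000 enrolled |
|---|---|---|---|---|
| 2% | 1.02 | 58.8% | 1.2 | 61 |
| 5% | 1.05 | 57.0% | 3.0 | 158 |
| 7% | 1.08 | 55.8% | 4.2 | 226 |
| 10% | 1.11 | 54.0% | 6.0 | 333 |
| 20% | 1.25 | 48.0% | 12.0 | 750 |

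For scale, the standard error of a 60% share at n = 3000 is √(0.6 × 0.4 / 3000) = 0.0089, or 0.9 points. The shift exceeds one standard error even at f = 2%, and is more than three standard errors at f = 5%. A larger registry would not reduce it.

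**Geographic comparison.** If f were the same in every region, all regional shares would be inflated by the same factor and their ratios would be preserved. If f differed, they would not. Take two regions with the same true share of 50%, one with f = 2% and one with f = 20%. The registry would show 0.50 / 0.98 = 51.0% and 0.50 / 0.80 = 62.5%, a difference of 11.5 points produced by entry alone. This shows the mechanism at the ends of the assumed range and is not an estimate.

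**The case against.** The strongest reply is that this is a mismatch of wording in a descriptive, hypothesis-generating registry, that its size cannot be derived from the documents, and that several larger readings fail. Most of this stands.

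- **A reader might infer that all non-operated patients are excluded.** They are not. Diagnostic instrumentation is an entry route of its own, so a patient who enters that way and is then observed or treated systemically is in the registry. Selection on management is therefore partial.
- **A reader might take the metastatic share in the Background as the excluded fraction:** "Metastases are found in 7% of all patients with UTUCs". The documents do not support this. The figure describes all UTUC, metastatic patients may still be instrumented or operated on, and the article does not say how many are not. Multiplying 7% by the number enrolled would also count excluded patients among those who got in. The 7% row in the table above is only one point in an assumed range.
- **A reader might infer from the Discussion that the non-surgical share differs by region.** The Discussion speaks only of regional variation in standard of care and access to care. That f varies with access is a plausible inference, not a statement of the plan.
- **A reader might extend the problem to all comparative results.** Complications by type of treatment, and recurrence after kidney-sparing treatment, radical nephroureterectomy or segmental ureterectomy, are compared among treated patients. The missing group belongs to none of those arms.
- **A reader might object that suspected and confirmed disease are mixed.** Prospective enrolment has to begin at suspicion, pathology is collected, and the choice of confirmed cases for an outcome analysis can be left to the analysis plan. It is no part of this point.

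What the reply does not answer is the contradiction itself. The article states both a scope and an eligibility rule, and they disagree about the population behind the primary objective. Condensing a longer protocol does not explain that.

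**Conclusion.** The point holds in a limited form. The article claims coverage irrespective of management, a property that its entry rule does not give it. Relative to the stated population, the share scheduled for neither instrumentation nor surgery is zero by construction, and shares of all other pathways are inflated by 1/(1-f). For an assumed f of 2% to 20% the factor is 1.02 to 1.25; the true f is unknown and cannot be obtained from the documents.

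The conclusion rests on reading Participant Characteristics as the operative rule, and on f being above zero. Distortion of the geographic comparison needs the further assumption that f varies by region. The results affected are mainly the descriptive treatment shares, guideline compliance, and any overall survival figure presented as applying to all UTUC. Severity is moderate: the claim should be corrected, but the data collected remain usable for the population actually enrolled.

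**What to change.** Reconcile the Abstract (Methods), Objectives and Study Design with Participant Characteristics:

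1. Define the population throughout as patients with suspected UTUC scheduled for upper-tract instrumentation or surgery.
2. Remove the phrase "irrespective of type of management" from the abstract and the matching words on type of treatment from Study Design.
3. State under Objectives, and wherever results are reported, that treatment shares, geographic patterns and guideline compliance are conditional on that entry criterion.
4. Name the absence of patients managed with neither as a limitation in the Discussion, and say that its size, and whether it varies by region, are unknown.

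This needs no new data and no change to enrolment. With 2451 of up to 3000 patients already included, correcting the claim is more practical than changing who may enter. The price is a narrower claim of generalizability. The selection remains, but readers will know which population the shares describe.

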### Data Collection and Analysis

Data from all participating centers will be collected through electronic case report forms by using an online data management system (DMS). The DMS is a Web-based system, which makes it convenient for participants worldwide to use, and multiple users of the same institution can be connected to the same data. The DMS is located and maintained at the CROES Office. A more detailed overview of the CROES DMS is provided in Multimedia Appendix 1 [33,34].

Local sites will fill out the electronic case report forms in the DMS prospectively and continuously over time and at the appropriate time. The correspondent local principal investigator is responsible for the reliability of the data and for controlling the accuracy of data. Patient data entered in the DMS was coded, and according to the European General Data Protection Regulation that went "into force" in May 2018, that data is pseudonymized. This means that only the controller (principal investigator responsible for the respective center) can link the code to the patient for audit purposes and follow-up data provision. The identity of the patients is not accessible through the CROES-DMS.

The DMS provides detailed overview reports of included data and runs queries to check for data inconsistencies and outlying values in order to ensure a reliable high-quality dataset. To minimize missing data, the CROES Office sends updates of the database to the principal investigator and is responsible for sending reminders to encourage provision of missing or follow-up data. The managers of the CROES office are in charge of monitoring the registry. Reports are regularly made to the steering committee. Data inconsistencies will be addressed by the local principal investigator, and decisions will be made by the steering committee on a case-by-case scenario.

Essential data elements aim to capture the multiple dimensions of the condition, from diagnosis to survival outcomes; baseline characteristics; risk factors; imaging and clinical assessment; management; complications up to 30 days after intervention; and survival data at 1, 3, and 5 years.

Data variables included in the electronic case report forms are categorized into six domains: general data, pretreatment assessment, treatment, pathology results, postoperative course, and follow-up. Each domain includes multiple variables.

All variables are defined, and they can be categorical (including descriptive, eg, type of complication for rare complications) or continuous. The variables collected include demographic and clinical patient characteristics, risk factors and symptoms, imaging and laboratory tests, treatment type, and pathological and survival outcomes. The key variables are described in Textbox 1.

Domains, key variables, and total number of variables in the UTUC-CROES registry.General data (number of variables=71)
Patient demographicsMedical and family historyRisk factorsSymptomsMedication (anticoagulants)
Pretreatment assessment (number of variables=80)
Imaging (local, regional, and distant)CystoscopyCytologyClinical tumor, node, and metastasis stage
Treatment data (number of variables=141)
Use of antibiotic prophylaxisTreatment typeIntraoperative detailsInstrumentation detailsNeoadjuvant treatment
Pathological data (number of variables=44)
Grade and Stage (2016 World Health Organization International Society of Urologic Pathologists)Pathological Stage
Perioperative data (number of variables=29)
Use of antibioticsComplications up to 30 days (number and type)Clavien-Dindo classification complicationsUse of intravesical instillationIndication for adjuvant therapy
Follow-up (number of variables=76; 76 variables per follow-up domain (maximum 5-year follow-up). Maximum of 21 follow-up visits possible in the data management system per patient.
Survival statusPresence of recurrenceLocation of recurrenceDiagnostics performedResults of the diagnostics
Total variables (number of variables=441)

As described in the operational flow diagram of the registry, the CROES statisticians will perform statistical analysis after data audit and data cleaning. The analysis will be performed after identification of specific objectives and attaining study approval from the steering committee.

Descriptive statistics will be used to summarize the data. Results will be presented in tables reporting at least the number of subjects, mean, SD, and minimum and maximum for continuous data and the number of subjects and percentages for categorical data. For testing, a significance level of 5% will be maintained, and all tests will be two-sided.

All analyses will be carried out on available data, and proportions of missing data will be reported. All analyses will be performed using SPSS version 25 (IBM Corporation, Armonk, New York) or R studio (RStudio Team, Boston, Massachusetts).

Multivariable analyses will be performed to assess possible associations with geographical or ethnic differences and risk factors for complications after surgery. The methodology will address potential sources of bias. When necessary, sensitivity analysis will be conducted. We will not use external data sources for comparison unless they are considered to be of outmost importance for specific objectives.

After closure of the primary inclusion process, an audit will be planned. The audit will focus on data source verification of the values of the identified critical variables and on internal consistency by cross checking among exclusive variables.

